### Statistical analysis

The analysis will be focussed on demonstrating, by analysis of covariance, any improvements at each follow-up, comparing the two groups, adjusted for the baseline level. The effect attributable to the intervention will be estimated by comparing differences in degree of improvement between the groups and the 95% confidence intervals will be calculated. The comparisons will be adjusted for potential confounding factors, by stratified analysis and statistical models, linear for continuous variable outcomes and logistic for dychotomic variables. In order to analyse the overall evolution in the course the one year of monitoring, the time effect on three repeated measures taken for each subject will be estimated, using mixed linear regression models with fixed effects (time, intervention, interaction between time and intervention) and randomised (specific effect of each subject and centre on the baseline level and the effect of time). These models will take into account the longitudinal structure of the three repeated measurements, as well as the hierarchical and multicentre structure of the data. These models will be extended to adjust for hypothetical prediction and modification variables of effect: age, sex, risk factors and comorbidity. All the analysis will be carried out using the SAS statistical package.

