On the other hand, physical exercise per se has been shown to be a safe intervention for people suffering from HF. This assertion has been supported by the recent HF-Action study, the largest clinical trial carried out on 2331 people with HF in NYHA class II-IV, to evaluate the effect of aerobic exercise in such patients [16,17]. The study concluded that exercise has a small beneficial effect on mortality and hospital admissions. Based on this study, it is plausible to hypothesise that the great contribution of exercise may be reflected in functional capacity and quality of life. In this study, the "state of health" (quality of life, symptoms, physical and social limitations) greatly improved in only three months. At the time the difference between the groups for comparison was not considered to be clinically relevant and only a small effect, of less than two points, could be attributed to exercise. In subsequent follow-ups, this limited difference remained constant, throughout the three years of monitoring [16]. The authors admitted that the lack of further improvement in scores after three months may have been a reflection of the exercise intervention not having been optimal, and the fact that the long-term adherence to the exercise programme was low and that the usual care group increased its physical activity.

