### Outcome measures

These measurements are made by an interviewer blind to the group the patient has been assigned to.

*Primary outcome measure *(basal, 3, 6 and 12 months):

• Changes in health-related quality of life (HRQL) (SF36, Minnesota Living with Heart Failure Questionnaire - MLHFQ).

The HRQL questionnaire is measured blindly with self-administered questionnaires: the Spanish version of the SF-36 and MLHFQ. Both questionnaires will be filled out before and after the intervention. SF-36 generates an 8-dimension health profile and two summary scores for the physical and mental components. The 21 items from the MLHFQ record the perception of the patient in relation to how the HF affects the emotional, social, physical and mental dimensions of their HRQL. Both questionnaires have been validated in the Spanish population [20,21].

*Secondary outcome measures *(basal, 3, 6 and 12 months):

• Functional capacity, measured with the 6-minute Walking Test [22].

• Muscular strength, measured by dynamometry [23].

• Body composition (body fat and muscle percentage) [23].

• Structural changes in the heart (natriuretic peptide levels, prognostic factor) [24].

*Predictor or Confounding variables*: sex, age, comorbidity and risk factors.

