### Sample size

A total of 600 patients will be recruited, 300 per group. This simple size gives a statistical power of higher than 80%, to enable any difference between the control and the intervention group greater than 3 with respect to the primary outcome scale from the physical functioning SF-36 and MLHQ to be found to be significant, with a significance level of 5% using the two-tailed Student's t test (standard deviations obtained from prior studies with similar population to that of our project: SD = 10 points of the quality of life questionnaires SF-36 and MLHQ) [12,25,26]. Given other reports, it can be expected that the losses during follow-up will be around 20%, the correlation between the measurements of the same individual 0.6 and the correlation intracentre 0.01.

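### The mixed model that the abstract names for the group comparison is written in random-slope form without the baseline score; visit categories with baseline as covariate would avoid a distorted or less precise effect

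*Protocol article*

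**What the plan says.** The Outcome measures section schedules the quality-of-life questionnaires at four occasions: "basal, 3, 6 and 12 months". The Study design section says the blinded measurements are repeated three times, alongside monitoring at 3, 6 and 12 months.

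The Statistical analysis section describes two analyses.

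- **Analysis of covariance.** The analysis is to focus on this comparison of the groups at each follow-up, adjusted for baseline.
- **Mixed model.** For the course over the whole year, "the time effect on three repeated measures taken for each subject will be estimated, using mixed linear regression models with fixed effects" for time, intervention and their interaction. The random part is described as the "specific effect of each subject and centre on the baseline level and the effect of time". The model is to be extended with age, sex, risk factors and comorbidity. The baseline score is not in that list.

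The section does not give the form of time (linear or by visit), and does not say which term of the mixed model is the treatment effect. The Methods/Design part of the abstract says the groups will be compared by intention to treat with multi-level longitudinal mixed models, and does not mention analysis of covariance.

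**The concern.** A random effect of time for each subject, paired with a random effect on the starting level, is the usual description of a random intercept and slope. If visit were a set of categories with one observation each, a subject-specific effect per visit could not be separated from residual error. Linear time is therefore the natural reading, although it is not written down.

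A straight line suits an effect that grows steadily. It does not suit one that is reached early and then held. The supervised programme fills the first three months, and the Background reports of an earlier large aerobic-exercise trial: "In subsequent follow-ups, this limited difference remained constant, throughout the three years of monitoring". If the effect here took that shape, a slope or interaction coefficient would not describe it, and a model without the baseline score would estimate it less precisely than the analysis of covariance in the same section. What is at stake is the figure reported if the abstract's model supplies the main comparison.

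**Working it through.** **Inputs.** All from the Sample size section: "A total of 600 patients will be recruited, 300 per group"; a difference of 3 points; SD 10; "with a significance level of 5% using the two-tailed Student's t test"; about 20% loss, so 300 × 0.8 = 240 per arm; within-patient correlation r = 0.6. My assumptions: a step effect of 3 points at months 3, 6 and 12; the same correlation at all lags (compound symmetry); linear time where stated. Power is Φ(effect/SE − 1.96).

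**The plan's own figure.** The plan claims power above 80%. With 300 per arm, SE = 10 × √(2/300) = 0.816 and power is 95.7%. With 240 per arm, SE = 10 × √(2/240) = 0.913 and power is 90.8%. The claim reproduces, and nothing below changes it.

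**Benchmark: analysis of covariance at one visit.** Residual variance = 100 × (1 − 0.36) = 64, so SE = 8 × √(2/240) = 0.730. The expected difference is 3.0 at every visit, with power 98.4%.

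**Reading A: linear time, baseline among the outcomes (months 0, 3, 6, 12).** The arm differences are 0, 3, 3, 3.

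- Mean time 5.25; Sxx = 189 − 4 × 5.25² = 78.75; Sxy = 63 − 4 × 5.25 × 2.25 = 15.75.
- Slope = 15.75/78.75 = 0.20 per month; intercept = 2.25 − 0.20 × 5.25 = 1.2.

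| Month | True difference | Fitted difference | Gain implied by slope alone |
|---|---|---|---|
| 0 | 0 | 1.2 | 0 |
| 3 | 3 | 1.8 | 0.6 |
| 6 | 3 | 2.4 | 1.2 |
| 12 | 3 | 3.6 | 2.4 |

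The SE of the slope difference is √(2 × 40/(240 × 78.75)) = 0.0651, so the slope test has 86.7% power. With an assumed random-slope variance of 0.15 per month squared, the SE is 0.0740 and power is 77.1%.

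**Reading B: linear time, follow-ups only (months 3, 6, 12), no baseline covariate.** The differences are 3, 3, 3, so the interaction is 0 and the intervention term is 3.0.

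- Mean time 7; Sxx = 42.
- If time is counted from baseline, the intervention term is the difference extrapolated to month 0. Its variance per patient is 60 + 40 × (1/3 + 49/42) = 120, so SE = √(120 × 2/240) = 1.00 and power is Φ(3 − 1.96) = 85%.
- Read at months 3, 6 and 12, the fitted difference is 3.0 with SE 0.859, 0.787 and 0.900, giving about 94%, 97% and 92% power.

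**Cost of leaving out baseline, mean of the three follow-ups.** Without baseline the variance is 100 × (1 + 2 × 0.6)/3 = 73.3. With baseline as covariate it is 73.3 − 60²/100 = 37.3. The ratio is 73.3/37.3 = 1.96. Power is 97.0% against 99.97%.

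**The case against.** The strongest reply is that the section puts analysis of covariance first. That analysis gives a baseline-adjusted difference at each follow-up, recovers an effect reached by month 3 and uses baseline efficiently. The mixed model is introduced for the overall course. This stands. A reader might infer that the trial will lose or understate its month-3 effect, and the documents do not support that inference.

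Five further replies:

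- **Linear time is not stated.** True. With visit as categories, the same fixed terms give visit-specific differences and nothing is distorted. Reading A and the zero interaction in Reading B depend on linearity.
- **Three against four measurements.** A reader might see a contradiction. The Study design section makes the three follow-ups the most likely meaning, and the baseline level can mean the random intercept. What remains is that the baseline score is not named as a covariate.
- **No false null is to be expected.** Correct. In Reading A the slope test keeps 77% to 87% power. In Reading B a zero interaction rightly says that the arms did not diverge further, and the intervention term carries the effect. The 0.6 at month 3 is the slope's contribution only; the fitted difference is 1.8.
- **The plateau belongs to another trial.** Also correct. The protocol reports it as a precedent, together with possible reasons such as low adherence, and does not predict it here.
- **This is detail for an analysis plan.** Partly so: the coding of time may be settled in a document not shown. But the random effect of time, the covariate list and the abstract's choice of model are all on the page.

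**Conclusion.** The point holds in a limited form and is of moderate importance. The lead analysis in the methods is sound. The abstract, however, assigns the group comparison to a mixed model whose description suggests a linear slope and lists no baseline score.

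If time is linear and a 3-point effect is reached by month 3 and held, the size is as follows:

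- With baseline among the outcomes, the effect is understated at months 3 and 6 (1.8 and 2.4), overstated at month 12 (3.6), and the slope-implied 12-month gain is 2.4.
- With follow-ups only, the interaction is 0 and the intervention term has about 85% power against 98%.

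The near doubling of the variance of the mean effect does not need linear time. It needs only that baseline stays out of a three-follow-up model, with r = 0.6 at all lags. In every follow-up-only case shown, power for the intervention effect at the planned 3 points stays above the stated 80%. The risk is a misdescribed or less precise effect, not a failed trial.

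**What to change.** In the Statistical analysis section, specify the mixed model for the outcomes at 3, 6 and 12 months, with visit as a categorical factor, the baseline score as covariate, intervention, and visit-by-intervention. State that the effect is the adjusted arm difference at the visits, not a slope or an interaction coefficient. The mixed model then targets the same differences as the analysis of covariance.

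Make the abstract and the Statistical analysis section agree on which analysis leads the group comparison.

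The cost is wording and SAS code. All the data needed are already scheduled, and the sample size does not change.

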### Randomisation

This is carried out centrally, once all baseline measurements are taken, by phoning to the Primary Care Research Unit of Bizkaia, where the patient is registered and assigned to one of the two study groups in 1:1 ratio by block randomisation of n patients and stratified by health centres.

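### The ANCOVA at each follow-up leaves out health centre, the randomisation stratum, so its standard errors are slightly too wide; adding centre costs almost nothing

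*Protocol article*

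**What the plan says.** All references are to the protocol article, Methods/Design.

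- **Settings** names six primary health centres.
- **Randomisation** is 1:1, by patient, in blocks and "stratified by health centres".
- **Statistical analysis** sets out the comparison at each follow-up "by analysis of covariance, any improvements at each follow-up, comparing the two groups, adjusted for the baseline level", then adds adjustment for potential confounders. **Outcome measures** lists these as sex, age, comorbidity and risk factors. Centre is in neither place.
- The same section describes a mixed model for the whole year, with fixed time, intervention and their interaction. Its random part is the "specific effect of each subject and centre on the baseline level and the effect of time". So the mixed model carries centre as a random intercept and a random time slope.
- **Sample size** assumes 600 patients (300 per group), a difference of 3 points, "SD = 10 points of the quality of life questionnaires SF-36 and MLHQ", 20% loss, a within-patient correlation of 0.6 and an intracentre correlation of 0.01.

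**The concern.** When allocation is balanced within centres, differences between centres cannot contribute to the treatment contrast. If the model omits centre, that variation still sits in the residual variance. The model-based standard error then overstates the true one, intervals are a little too wide, and the test rejects slightly less often than its nominal 5%. The usual remedy is to analyse by the factor used to stratify. Here the adjustment set in the text omits that factor, while the mixed model in the same section includes it, so the two analyses treat centre differently.

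A lesser concern is the mixed model. It estimates two centre-level variances from six centres, which leaves 5 degrees of freedom for each, and the plan expects the intercept component to be very small. A variance estimated at zero or a singular fit is then a realistic outcome. Without a stated fallback, the model would be revised after the data are seen.

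**Working it through.** **Inputs from the article.** 300 per group; 20% loss, so 0.8 × 300 = 240 analysed per group; SD 10; difference 3; two-sided 5%; within-patient correlation r = 0.6; intracentre correlation (ICC) 0.01; six centres.

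**Assumptions.** Centres are of equal size, so 480/6 = 80 completers each. The ICC is applied to the baseline-adjusted residual. ICC values of 0.05 and 0.10 are shown as a range and are not in the plan.

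**1. The plan's own power figure (two-sample t test).** SE = 10 × √(2/n).
- n = 300: SE = 0.816; 3/0.816 = 3.67; power = Φ(3.67 − 1.96) = 95.7%.
- n = 240: SE = 0.913; 3/0.913 = 3.29; power = Φ(3.29 − 1.96) = 90.8%.

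The stated power above 80% is met, before and after loss.

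**2. ANCOVA without centre.** SE = √[2 × 100 × (1 − 0.6²)/240] = √(128/240) = 0.730.

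**3. ANCOVA with centre as a fixed effect.** The between-centre share of the residual is removed, so SE = 0.730 × √(1 − ICC). The SE without centre is too large by the factor 1/√(1 − ICC), and its true type I error is 2 × [1 − Φ(1.96/√(1 − ICC))].

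| ICC | SE without centre | SE with centre | Excess | Type I error without centre |
|---|---|---|---|---|
| 0.01 | 0.730 | 0.727 | 0.5% | 0.049 |
| 0.05 | 0.730 | 0.712 | 2.6% | 0.044 |
| 0.10 | 0.730 | 0.693 | 5.4% | 0.039 |

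At ICC 0.01, power for 3 points is about 98.5% with or without centre. A simulation of 4,000 trials per setting (blocks of 4 assumed, 20% random loss) agrees within its sampling error: mean SE 0.731 without centre and 0.727 with it, type I error 0.048 and 0.046.

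**4. Price of the five indicators.** Residual degrees of freedom fall from 477 to 472, and the critical t moves from 1.96495 to 1.96500.

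**5. Centre variances in the mixed model.** For one visit and a one-way layout, the intercept variance estimate is at or below zero with probability P[F(5, 474) < (1 − ICC)/(1 − ICC + 80 × ICC)].
- ICC 0.01: P[F < 0.99/1.79 = 0.553] = 26%.
- ICC 0.05: 3%.

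With three visits averaged, assume a centre variance of 1 that is stable over time, a between-patient variance of 59 and a residual variance of 40 (total 100, within-patient correlation 0.6). The within-centre variance of a patient mean is 59 + 40/3 = 72.3, the ratio is 1 + 80/72.3 = 2.11, and the probability is about 20%.

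For intercept and slope together, a moment-based simulation gives a singular matrix in about 44% to 84% of trials, for a centre slope SD between 2 and 0 points per year. The article gives no slope SD, so that range is an assumption.

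**6. Effect on the treatment contrast.** With variances taken as known (patient slope variance 4 and centre slope SD 1, both assumed), the between-arm SEs at 3, 6 and 12 months are 0.909, 0.913 and 0.926. They agree to three decimals whether centre intercepts and slopes are random or fixed, because the arms are balanced within centre.

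**The case against.** The strongest objection is that this is a condensed article and the ANCOVA covariate list is not closed. It allows for potential confounders, it never says centre is excluded, and the plan clearly has centre in mind: it stratifies by it, quotes an intracentre correlation and includes it in the mixed model. If the mixed model is the main analysis, centre is already there. The effect is also tiny at the planned ICC. The point about size stands. The point about omission stands only in part: the article does say what the ANCOVA adjusts for and does list the confounders, and centre is in neither place.

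On the mixed model, the objection largely succeeds. A reader might infer that six centres cannot support the random centre effects at all, or that fixed centre effects are simply better in both analyses. The document supports neither. The variances are identifiable on 5 degrees of freedom, though very imprecisely. A zero estimate removes a term that was expected to be small and leaves the treatment contrast practically unchanged. Random or fixed centre is a choice on which reasonable statisticians differ.

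A reader might also think that treatment inference should use a critical value of 2.57 (t on 5 degrees of freedom) instead of 1.96. That could concern only change within an arm: the planned model has no random centre-by-intervention term, so the between-arm contrast is not tied to 5 degrees of freedom.

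**Conclusion.** The point holds for the visit-wise ANCOVA and is minor. As written, its adjustment set omits the randomisation stratum, and its standard errors are about 0.5% too wide at the planned ICC of 0.01, rising to 2.6% at 0.05 and 5.4% at 0.10. The error is towards conservatism. There is no bias, no invalid test and no change to the sample size. These figures rest on equal centres, 20% loss and the ICC applying after baseline adjustment; if baseline already explains part of the centre differences, the excess is smaller.

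The remark on the mixed model is optional. Boundary or singular fits are quite likely under the plan's own ICC, but they have practically no effect on the between-arm estimate. The benefit of dealing with them in advance is a model that need not be chosen after seeing the data.

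**What to change.** Add centre as a fixed effect (five indicators) to the ANCOVA at each follow-up, beside the baseline value. This takes one line of text and 5 degrees of freedom out of about 480 patients.

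Optionally, state in advance what happens if the random centre terms in the mixed model give a zero variance, a singular matrix or no convergence. One suitable fallback is fixed centre terms, with the within-patient correlation kept. Five indicators replace only the random centre intercept. If the centre-specific time effect is to be kept, centre-by-time terms are needed too, at about 5 more degrees of freedom for a linear slope. Inference on change within each arm would then refer to these six centres.

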### Quality control

Various processes were undertaken in order to guarantee the quality of the data of the study, and thus maximise the validity and reliability of the programme and measurement of outcomes. These are:

• Preparation of documents for the study process: fieldwork manuals, nursing and intervention measurements, educational leaflets and list of measurements.

• Written documentation: electronic and hard copies of the protocol, signed consent forms, and patient results stored under lock and key. All written information, including letters sent to patients is standardised in each of the centres.

• Training for those in charge of the standardisation of the study process.

• Training for nurses concerning the study characteristics and procedures, and, in particular, the quality of life interview to be given to the patients.

• Holding of regular meetings: with the coordinator of the study (daily) and with the principal investigator of each collaborating centre (weekly).

• Quarterly meetings and daily contact by email with the members of the EFICAR group and all the participating centres.

• Monthly production of progress reports.

### Ethical and legal aspects

This study complies with the Declaration of Helsinki and subsequent revisions as well as with correct clinical practice.

Data confidentiality: only the researchers involved with this study have access to data concerning the individuals who have agreed to participate in the study.

The following documents have been obtained:

• Approval of the Ethics Committee and the Spanish Personal Protection Act according to the Act 15/1999 and recent regulation (RD 1720/2007).

• Report from the research commission.

• "Understanding and commitment to collaborate from the services involved" signed by the legal representative of each Centre.

### Limitations

Despite the study not dealing with mortality and hospital admissions as a main measure, it is important to highlight that the HF-Action study has demonstrated that the effect of exercise on mortality is minimal. Given this, the functional capacity and quality of life are the most important aspects to improve in the rehabilitation of these patients.

Also, the structure of the study renders impossible blinding the participants and the interveners, however, blind outcome assessors will be used.

The monitoring of this intervention and data collection is complex, and therefore data will be collected using many relevant quality control processes, and standardization of the intervention will be assured. In addition, to avoid contamination of the control group, interveners will be trained, and a pilot study will also be carried out.

